### Dissemination

The results for the primary and secondary outcomes of this RCT will be shared regardless of the direction or magnitude of the effect. These outcomes are planned to be published in international high-quality, peer reviewed journals. Results will also be presented at national and international conferences as well as used for teaching purposes to community and university led forums.

## Discussion

To the best of our knowledge this will be the first RCT to examine the benefits of a structured, supervised exercise intervention in AYAs from their cancer diagnosis and throughout their subsequent treatment. Furthermore, it will be the first RCT to explore the potential impact that exercise has on patient-reported treatment-related toxicities. In addition, we will explore any relationship evident between changes in physical functioning and patient-reported treatment-related toxicities.

The design of this study represents both a strength and potential weakness. While a control group is essential to be able to determine any impact that exercise has in the intervention group, the research team deems it unethical to actively encourage sedentary behaviour. In order to address this, the cross over design allows for both groups to be exposed to the exercise intervention and will determine the most appropriate timing for the intervention. Additionally, both groups will be asked to record any physical activity they complete throughout the trial which will be accounted for as potential covariate in the final analysis. Nonetheless, the crossover design will also permit an ability to evaluate any changes in exercise-related beliefs or practices in the immediate exercise group, following their initial 10-week exercise programme.

If it is demonstrated that this exercise intervention prevents functional decline associated with cancer treatment in AYAs, then such programmes can be adopted widely in this cohort. Further, this research will allow clinicians to better understand the potential benefits of exercise on mitigating treatment-related toxicities encouraging targeted research by toxicity, aiming to improve overall treatment tolerance in AYAs.

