**Methods/design:**

A total of 40 AYAs recently diagnosed and due to commence systemic treatment (± 2 weeks) for a primary haematological malignancy or solid tumour will be recruited and randomised to either an immediate exercise intervention or usual care (delayed exercise) for 10 weeks. This randomised controlled crossover trial will see both groups engage in a supervised exercise intervention from either diagnosis (baseline assessment) for 10 weeks (0–10 weeks) or following an interim assessment to 20 weeks (10–20 weeks). The bi-weekly tailored exercise programme will combine aerobic and resistance exercises and be supervised by an Accredited Exercise Physiologist. Participants will complete a range of assessments at 0, 10, and 20 weeks including cardiopulmonary exercise tests, 1 repetition maximum strength measures, physical functioning, and self-reported quality of life measurements. Patient-reported treatment-related toxicities will be recorded on a weekly basis.

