Over the last three decades, evidence supporting the integration of exercise in cancer cohorts has grown exponentially [14–16]. It is now accepted that appropriately tailored exercise is safe and tolerable in a wide range of cancer cohorts, with national and international bodies calling for exercise to be embedded into standard cancer care [15, 17, 18].There is strong evidence that exercise mitigates the known effects of cancer treatments including cancer-related fatigue, muscle wasting, cardiorespiratory decline and psychological distress [19–21]. However, this research is primarily in adult and paediatric cohorts, with a paucity of high-quality evidence available in AYA-specific populations [22]. Several small, single-centre, non-randomised studies and reviews have demonstrated some benefits on the prevention of functional decline, reduction in fatigue and on quality of life variables in AYAs [23–26]. However, while these results are promising, it is recognised that they need to be further explored in a high-quality, randomised controlled trial [22].

In order to address the distinct lack of understanding of integrated exercise on functional capacity and treatment toxicity management in AYAs during cancer treatment, we developed this randomised controlled trial. The primary aim of the study is to determine whether a 10-week individualised exercise intervention is associated with a reduction in the decline of physical fitness (V0_2peak_) experienced by AYAs during cancer treatment, when compared with controls. Secondary aims are to assess the effects of the intervention on muscular strength, body composition, functional capacity, treatment-related toxicities and psychosocial variables. The purpose of this paper is to detail the FiGHTINGF!T study design and protocol based on the Standard Protocol Items for Randomised Trials (SPIRIT) guidelines.

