## Methods

### Study design

The FiGHTINGF!T trial is a prospective, single-centre, randomised controlled (RCT) cross over, superiority trial. Following baseline assessments, participants will be randomised to either immediate exercise or delayed exercise (usual care) for an initial period of 10 weeks. Following an interim assessment at 10 weeks, participants will cross over to the opposing group and either commence exercise (delayed exercise group) or commence usual care. There will be no wash out period between groups. The study is registered at the Australia New Zealand Clinical Trial Registry (ANZCTR) (ACTRN12620000663954) with participant recruitment for the trial now initiated. Proposed study activities are outlined as per SPIRIT guidelines (Table 1; Additional file 2). The RCT will be conducted over 3 years at the Sir Charles Gairdner Hospital, Perth, Australia. Figure 1 depicts the study design as per the CONSORT guidelines for randomised crossover trials [27].

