#### Immediate exercise group

These participants will commence their exercise programme the week following their baseline assessment and will be required to attend two supervised exercise sessions per week for 10 weeks. Sessions will be approximately 60 min in duration and scheduled at appropriate times relative to participants’ treatment schedules, with exercise conducted prior to or > 24 h following chemotherapy administration. This scheduling strategy is aimed to maintain participant safety, as well as to reduce the burden of additional appointments and limit inconvenience to the participant. Participants will complete a post-intervention assessment at 10 weeks. Following the 10-week interim assessment, participants will then receive no further structured supervised exercise intervention for the remaining 10 weeks, prior to the subsequent final assessment at 20 weeks.

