#### Delayed exercise intervention (usual care)

These participants will not be offered any exercise intervention for the initial 10 weeks following baseline assessment. There will be no specific exercise prescription provided to the participants other than that contained in generic information provided by treating teams to all patients as part of the usual standard of care. Participants randomised to this treatment arm will also complete an interim assessment at 10 weeks. Following the interim assessment, participants will then commence bi-weekly supervised exercise sessions for 10 weeks reflecting that offered to the immediate exercise group. Participants will complete final assessments at 20 weeks.

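### For VO2peak and the other fitness outcomes, the crossover schedule cannot show when exercise is best started, although the Discussion says that it will

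*Protocol article*

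**What the plan says.** The protocol article presents the timing question as something the design answers. In the Discussion, as part of the argument for a crossover: "the cross over design allows for both groups to be exposed to the exercise intervention and will determine the most appropriate timing for the intervention". The sentence carries no qualification and is not limited to any outcome.

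The schedule is set out in Methods:

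- Under Immediate exercise group, once the week-10 visit is done: "participants will then receive no further structured supervised exercise intervention for the remaining 10 weeks, prior to the subsequent final assessment at 20 weeks".
- For the other arm, under Delayed exercise intervention, once the same visit is done: "participants will then commence bi-weekly supervised exercise sessions for 10 weeks reflecting that offered to the immediate exercise group". Its last assessment is also at week 20, directly after training.
- Study design: "There will be no wash out period between groups".
- Abstract, Methods/design: "Participants will complete a range of assessments at 0, 10, and 20 weeks". No later visit is described.

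The primary aim, in Background, is whether a "10-week individualised exercise intervention is associated with a reduction in the decline of physical fitness" compared with controls. Neither the primary nor the secondary aims mention timing.

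**The concern.** At the only visit after both arms have trained, they differ in two ways at once: when they started, and how long ago they stopped. Any fitness lost after supervised training ends lowers the immediate arm at week 20 and leaves the delayed arm untouched. A reader who takes the Discussion at its word could read such a difference as evidence for a later start when it reflects only the assessment date.

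An analysis plan cannot repair this. The two factors are tied by the visit schedule, since no visit finds the delayed arm 10 weeks past its own training. What is at stake is the interpretation of the second period and of week 20, not the primary comparison at week 10.

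**Working it through.** **Inputs.** Effect size 0.80 and SD 3.6 ml/kg/min (Statistical consideration), used only for illustration. Visits at 0, 10 and 20 weeks, with no washout. The fraction of benefit still present 10 weeks after supervised training ends, r, is not given in the article; it is assumed to lie between 0 and 1. The plan states no figure for a timing effect, so there is none to reproduce.

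**Model.** Let start time make no difference: each programme yields the same benefit B at its end, measured against the course without training, which randomisation makes the same on average in both arms.

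B = 0.80 × 3.6 = 2.88 ml/kg/min.

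| Week | Immediate | Delayed |
|---|---|---|
| 0 | 0 | 0 |
| 10 | B | 0 |
| 20 | rB | B |

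**Contrast 1: week 20, delayed minus immediate.** B − rB = (1 − r)B. The last column is the chance of p ≤ 0.05 in a two-sided two-sample t-test with 20 per arm and SD 3.6.

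| r | Difference, SD | Difference, ml/kg/min | Chance of p ≤ 0.05 |
|---|---|---|---|
| 1 | 0 | 0 | 5% |
| 0.75 | 0.2 | 0.72 | 9% |
| 0.5 | 0.4 | 1.44 | 23% |
| 0.25 | 0.6 | 2.16 | 46% |
| 0 | 0.8 | 2.88 | 69% |

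The difference favours delayed exercise for every r below 1, although start time has no effect in this model.

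**Contrast 2: difference between arms in 10-week change.** Weeks 0–10: B = 2.88. Weeks 10–20, delayed minus immediate: B − (rB − B) = B + (1 − r)B, which is 2.88 at r = 1, 4.32 at r = 0.5 and 5.76 at r = 0. The second-period figure is inflated because its comparator is losing earlier gains.

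**Contrast 3: each arm at the end of its own programme (immediate at week 10, delayed at week 20).** Time since training is now equal. But one value follows about 10 weeks of cancer treatment and the other about 20, and the effect of treatment itself on fitness has to be subtracted. At week 10 the delayed arm is an untrained concurrent control. At week 20 there is none, because the other arm has already trained.

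**Contrast 4: mean VO2peak over weeks 0–20 (trapezoid rule).**

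- Immediate: [10(0 + B)/2 + 10(B + rB)/2] / 20 = B(0.5 + 0.25r)
- Delayed: [0 + 10(0 + B)/2] / 20 = 0.25B
- Immediate minus delayed: 0.25B(1 + r)

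With B = 0.8 SD this is 0.2 SD at r = 0, 0.3 SD at r = 0.5 and 0.4 SD at r = 1. This summary favours early exercise at every r, again with no true effect of start time. At r = 0.5 it favours immediate exercise by 0.3 SD while week 20 favours delayed exercise by 0.4 SD. The same data from the same model can therefore point either way, depending on the summary chosen.

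**The case against.** Several points can fairly be made for the article, and most of them stand.

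- **A reader might infer that week 20 is the planned test of timing.** The article does not say so. Timing is not a listed aim, and Statistical consideration names general methods without assigning a contrast to this question. The criticism is of the Discussion's claim, not of a specified analysis.
- **A reader might infer that the bias is as large as the effect the trial is sized for.** That holds only at r = 0, complete loss, and nothing in the article supports that value. Exercise prescription encourages aerobic activity outside the sessions, which could raise r. The Discussion plans to use recorded activity as a potential covariate and to look at changed exercise practices in the immediate arm, which may help describe retention.
- **A reader might infer that the trial can say nothing about timing.** That is too strong. Adherence is a declared feasibility outcome (Feasibility), and it can be compared between randomised start times without any detraining problem. Toxicity is recorded weekly, so its 20-week total is a randomised comparison of the two strategies.
- **Week 20 is not invalid.** It is a proper randomised comparison of fitness status under two 20-week strategies.
- **A reader might infer that services would be steered away from early exercise.** The Discussion ties wider adoption to whether the programme prevents functional decline, not to a timing result.

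None of this rescues the statement for fitness outcomes. It says without reservation that the design will settle the timing, and no contrast available on VO2peak does so.

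**Conclusion.** The timing claim is wrong as written for VO2peak and the other fitness outcomes. With equal true benefit at either start, week 20 could favour delayed exercise by 0.8 × (1 − r) SD, anywhere from 0 to 0.8 SD, and by 0.4 SD if half the gain remains. The direction follows from the schedule whenever some gain is lost; the size rests on r, which is an assumption, and on the planning effect size of 0.80.

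The defect is confined to what is said about timing. The week-10 comparison of exercise with usual care is randomised, has a concurrent control and is unaffected.

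**What to change.** 1. In the Discussion, delete the timing claim or narrow it to what the design can show.
2. Describe week 20 as a randomised comparison of two 20-week strategies with unequal time since training, and state that it is not interpreted as an effect of start time.
3. Limit any statement on timing to contrasts free of detraining, such as adherence by start time. Report cumulative toxicity over 20 weeks as a comparison of strategies.
4. If a mean VO2peak over weeks 0–20 is reported, label it a strategy summary too. It is no remedy for the timing question, because it leans towards early exercise for the reason shown above.

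The cost is a narrower stated claim. No new data, visits or participants are needed.

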### Intervention

All participants will complete baseline assessments and be randomised prior to commencing (± 2 weeks) systemic treatment. All exercise programmes will be individually prescribed by an Accredited Exercise Physiologist (AEP) and tailored relative to each patient’s presentation. The programmes will follow the American College of Sports Medicine (ACSM) and Exercise and Sports Science Australia (ESSA) guidelines for combined aerobic and resistance exercise for cancer patients [16, 21]. All exercise sessions will be undertaken in a one-on-one basis within a purpose-built gymnasium in the hospital setting and will be supervised by an AEP. No concomitant care or therapies will be specifically permitted (or prohibited) during the trial. However, it is anticipated that participants may exercise outside of the trial, and therefore, all participants will be asked to complete an activity journal to capture any incidental exercise they may perform. The contents of the journal will be checked on a weekly basis by members of the research team. This weekly monitoring will also ensure participants are adhering to the study protocol and associated invention requirements.

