#### Exercise prescription

All exercise sessions will be multi-modal and follow the same format throughout the 10-week intervention. Participants will commence each session with a 5-min warm up, followed by aerobic bouts, a resistance training component and concluding with a 5-min cool down and static stretching period of major muscle groups. The aerobic component of the programme will be based on the participant’s physical capabilities and preference of the modalities available within the gym (including cycling on an upright/recumbent bike, treadmill walking/jogging and/or skipping) and aim to accumulate 20–30 min at moderate intensity over the duration of the session. Intensity will be monitored using heart rate (HR) and rating of perceived exertion (RPE) [28]. Moderate intensity aerobic exercise is considered 60–85% of maximal heart rate (220 − age) [29] or an RPE of 12–14. Participants who are unable to complete 20 min continuously will aim to accumulate the required load in bouts of 5 to 10 min as tolerated. The resistance training component will comprise of 6–8 exercises targeting the major muscle groups of the body. Participants will complete 2–4 sets of 8–15 repetitions, at 60–80% of 1 repetition maximum (1RM) or an RPE of 12–14 [29]. Based on the thorough baseline assessment, any pre-existing injuries or treatment-related effects will be considered when prescribing and progressing all exercises. The sessions will aim to increase in exercise intensity as tolerated. Participants will also be encouraged to engage in aerobic exercise outside of supervised exercise sessions and asked to document their activity in exercise journals to meet exercise recommendations for cancer survivors [16, 21]. Exercise programmes will be modified on a weekly basis as required relative to participants’ treatment schedules and related side effects, as well as changes in their individual physical conditioning throughout the programme. Participants’ vital signs and most recent full blood picture will be reviewed prior to commencing each and every exercise session, to determine their safety for exercise and any need for programme modification as per published guidelines [30]. In the unlikely event any injuries occur during exercise sessions, these will be documented accordingly, and participants will be offered appropriate medical treatment/care without any cost to them.

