### Statistical consideration

A total of 40 participants will be recruited, evaluated and analysed as part of this study. Analysis will be performed using an intention to treat approach [43]. A power analysis using PS Power and sample size calculations Version 3.1.2 has been performed to calculate the sample size required for this study, based on the primary outcome variable VO_2peak_ (ml kg min^−1^). In the absence of comparable published data in AYA patients, similar studies undertaken by Thorsteinsson et al. [44] and West et al. [45] in paediatric and adult patients demonstrated an effect size of 0.80. The standard deviation across multiple studies utilising VO_2peak_ as the primary outcome measure varies from 1.5 ml kg min^−1^ to 5.7 ml kg min^−1^, and therefore, a median value (3.6 ml kg min^−1^) has been utilised for this trial sample size calculation. Assuming a 5% significance level and a power of 0.8, a sample size of 36 patients (18 per group) will be required. An additional 10% has been included (*n*=4) to allow for attrition or unusable data. An interim analysis is planned following 50% of participant recruitment to investigate outcomes between groups.

Both interim and final analysis will employ standard descriptive statistics (M, SD, *n*, %) to summarise data on participant demographics and recruitment rates. Outcome analyses will include Student’s *t*-test, chi-square, correlation, regression and repeated measures ANOVA where relevant to examine differences between groups in the nominated variables, as well as the overall change scores over time. Further statistical analysis will be employed to investigate any associations between exercise-related changes and TRTs. Any clinically relevant covariates will be included in the analyses. All statistical analyses will be conducted using SPSS software (version 20.0, IBM, Armonk, NY, USA) and significance will be set at *p*≤0.05.

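### Physical activity recorded after randomisation is proposed as a possible covariate for the final analysis, and nothing keeps it out of the efficacy models

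*Protocol article*

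**What the plan says.** The design paragraph of the Discussion states that both groups will record "any physical activity they complete throughout the trial which will be accounted for as potential covariate in the final analysis". The reason given is that the team will not encourage inactivity in controls, so some control participants may exercise.

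The other relevant statements are in the Methods:

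- Intervention: "all participants will be asked to complete an activity journal to capture any incidental exercise they may perform". The journals are checked weekly.
- Exercise prescription: "Participants will also be encouraged to engage in aerobic exercise outside of supervised exercise sessions", and this activity is to be written in the journals.
- Delayed exercise intervention (usual care), first 10 weeks: "There will be no specific exercise prescription provided to the participants other than that contained in generic information" from the treating teams.
- Statistical consideration: "Any clinically relevant covariates will be included in the analyses". No restriction to baseline variables follows. The same section says: "Analysis will be performed using an intention to treat approach".

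The primary aim, in the Background, is to "determine whether a 10-week individualised exercise intervention is associated with a reduction in the decline of physical fitness" in comparison with controls.

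**The concern.** A covariate in a randomised comparison is safe when treatment cannot have affected it. On-trial activity does not meet that condition, because randomisation follows the baseline assessment and the journal runs afterwards. The programme also tries to raise this activity in the exercise arm. Outside aerobic exercise is a plausible route to better VO2peak, so holding it constant removes part of what the intervention is meant to do.

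There is a second problem. A patient who tolerates treatment well is likely both to move more and to keep more fitness. Conditioning on activity then links arm with tolerance, and the adjusted coefficient is neither the total effect nor a clean direct effect.

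What is at stake is the meaning of the treatment estimate in a trial of 40 participants. A choice about adjustment that is left open until the data are in could move the result either way.

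**Working it through.** **1. Position of the variable.** Study design places randomisation after baseline, and Intervention places the journal during the trial. Exercise prescription promotes outside activity as part of the programme, and the delayed group has no matching prescription in weeks 0 to 10. The Discussion also proposes to evaluate how exercise practices change in the immediate group after its programme, so the article itself treats later activity as something the intervention may alter. No section confines the activity adjustment to a sensitivity, mediation or exploratory analysis.

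**2. Inputs.** The plan gives no between-arm difference in activity and no slope of VO2peak on activity, so there is no figure of its own to reproduce on this point. From Statistical consideration I take the effect size 0.80, read as standardised, and the SD of 3.6 mL/kg/min: 0.80 × 3.6 = 2.88 mL/kg/min. Everything else is assumed.

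**3. Model** (SD units; T = arm, M = on-trial activity, U = unmeasured common cause with variance 1):

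- M = a·T + u·U + error with variance s²
- Y = d·T + b·M + u·U + error
- total effect = d + a·b
- arm coefficient after adjusting for M = total − a·[b + u²/(u² + s²)]

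**4. Illustration**, with total = 0.80, a = 0.5, b = 0.3:

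- No common cause (u = 0): 0.80 − 0.5 × 0.3 = 0.65, a change of −0.15/0.80 = −19%.
- Common cause u = 0.5, s² = 1: 0.25/1.25 = 0.20, so 0.80 − 0.5 × 0.50 = 0.55 (−31%).
- Common cause u = 0.5, s² = 0.75 (within-arm variance of M equal to 1): 0.25/1 = 0.25, so 0.80 − 0.5 × 0.55 = 0.525 (−34%).

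Multiplied by 3.6, the total of 2.88 mL/kg/min becomes 2.34, 1.98 and 1.89.

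**5. Direction.** If controls are the more active arm (a = −0.5, total held at 0.80, no common cause), the coefficient is 0.80 + 0.5 × 0.3 = 0.95, or 3.42 mL/kg/min. With a = 0 it stays at 0.80 in every case.

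**6. Range without a common cause**, in mL/kg/min, from 2.88 − 3.6·a·b:

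| Activity shift a (SD) | b = 0.2 | b = 0.4 |
|---|---|---|
| −0.5 | 3.24 | 3.60 |
| 0 | 2.88 | 2.88 |
| 0.5 | 2.52 | 2.16 |
| 1.0 | 2.16 | 1.44 |
| 1.5 | 1.80 | 0.72 |

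A simulation of the same structure agreed with these values. In that simulation, adding a common cause that explained 30% of the within-arm variance of activity and had a loading of 0.4 on VO2peak took the last cell (a = 1.5, b = 0.4) to about −0.5.

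**The case against.** The strongest reply is that the article commits to little. It calls activity a potential covariate and does so in the Discussion. The statistical section never names activity. It lists t-tests, regression and repeated measures ANOVA where relevant, and an unadjusted comparison of VO2peak fits that text equally well. The general covariate sentence names no post-randomisation variable; it only fails to exclude one. The full protocol and any analysis plan are not shown and may settle the model. The purpose, to account for exercise among controls, is also legitimate.

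Much of this stands. A reader might infer that activity will be in the primary model and that the primary result will therefore be biased. The documents do not support that: the consequence holds only if activity is entered. A reader might also infer a bias towards no effect. That has no source either, because the direction depends on which arm turns out more active.

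A third tempting reading is that the adjustment breaches intention to treat. Intention to treat mainly means analysing everyone as randomised, and a covariate neither moves nor excludes anyone. The mismatch is with the quantity named in the primary aim.

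What does not stand is the idea that this is only missing detail. The article affirmatively proposes the variable for the final analysis and sets no limit on its role. Calling it potential is no safeguard if the choice can be made after the data are seen. Nor does regression on journal activity recover the effect that would be seen without control-group exercise.

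**Conclusion.** The point holds conditionally. The article proposes a post-randomisation variable, promoted by the intervention, as a potential covariate and does not keep it out of the efficacy models. If it is used there, the arm coefficient stops being the total effect of the 10-week programme against control, and shared causes of activity and fitness may bias it as well.

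The size and direction in this trial are unknown. The illustrated fall from 0.80 to 0.65 SD, or to about 0.53 to 0.55 SD with a common cause, rests on an assumed shift, slope and loading. It shows the mechanism and does not forecast the result. The estimate is inflated if controls are more active and unchanged if the arms do not differ in activity.

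**What to change.** State in the statistical section that covariates in the primary and secondary efficacy models are limited to values obtained before randomisation: the baseline value of the outcome, the treatment-intensity stratum and, if wanted, the baseline International Physical Activity Questionnaire score. Amend the Discussion sentence to match. Report journal and questionnaire activity during the trial by arm, as a description of contamination and adherence, or use it only in an analysis labelled exploratory.

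The cost is one sentence in the statistical section and a matching edit in the Discussion. It needs no new data and adds no burden for participants. It should be settled before outcomes are compared between groups.
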